## Abstract

**Background:**

Emotional resilience is a dynamic process by which individuals may prevent, overcome, and thrive following challenging events. Emotional resilience can be defined as absence of negative outcomes (ie, symptoms of psychopathology) and/or the presence of adaptive outcomes (ie, well-being). Despite the wealth of research tracking the nature of and contributions to emotional resilience in adolescence and adulthood, there is a dearth of evidence on the nature of resilience and its development during preadolescent childhood despite this being an important preventative period for later mental health difficulties and a period when emotional experiences change.

**Objective:**

Our primary study objectives are 3-fold: to explore how preadolescent children growing up in deprived areas of London may operationalize resilience, evaluate whether there are differences in the development or trajectories of resilience among our target population, and understand what contributes to resilience pathways over time. Additionally, our research aims to better understand the psychometric properties of resilience measures used in a preadolescent sample and assess the feasibility of developing a longitudinal cohort study of preadolescent children in East London.

**Methods:**

We will conduct an accelerated longitudinal cohort study in primary schools across the broad geographical area of East London. The multimethod approach will span across 3 data collection arms: (1) child cognitive tasks and psychometric questionnaires in classroom settings, (2) teacher ratings, including teacher assessments of school mental health provisions, and (3) parent questionnaires. We aim to recruit approximately 1200 children aged 7-11 years at baseline across UK school years 3, 4, and 5. Our measures will span themes of resilience and mental health, as well as personal, social, and community resources available to the children. We will collect quantitative data via questionnaires from children, their parents, and school staff. We will collect qualitative data from the children through paper-based tasks.

**Results:**

Study recruitment commenced in October 2022 and continued till December 2023. Baseline testing commenced in October 2022 and continued till December 2023; 873 students were enrolled at baseline. Follow-up is anticipated to continue at least annually until June 2027.

**Conclusions:**

This study will assess the feasibility of conducting a longitudinal cohort study on preadolescent children in East London. Alongside evaluating the psychometric properties of resilience measures used in this age group, this study will explore how resilience develops in children across time and relate this to other outcome measures. By identifying how personal, social, and community resources may affect resilience in preadolescent children, we will enhance the understanding of how emotional resilience develops in preadolescent children, and future studies will be able to develop interventions to boost resilience by targeting young and diverse populations.

**Trial Registration:**

ISRCTN ISRCTN12430839; https://www.isrctn.com/ISRCTN12430839

**International Registered Report Identifier (IRRID):**

DERR1-10.2196/70797

## Introduction

### Background

Resilience is a dynamic process that refers to the capacity of individuals to prevent, overcome, and even thrive following the experience of challenging events [1]. Resilience outcomes can be captured through functioning in different domains, but here, we focus on emotional resilience, which can reflect the presence of an adaptive outcome (well-being, life satisfaction) or the absence of a negative outcome (mental illness) [2] following the experience of stress (internal or external), which can range from adverse childhood events to ongoing chronic stressors. Resilience can be conceptualized as an individual characteristic (eg, grit, perseverance, determination), but it also includes opportunities to harness and navigate access to culturally relevant external resources (eg, contact seeking, participation in community groups) [3]. Although there is a growing body of literature measuring and tracking emotional resilience (good mental well-being and absence of psychopathology following stress) and the factors and resources that contribute toward it in adolescence [4,5] and young adulthood [6,7], there is notably less research on the nature of resilience and how and when it develops at even earlier stages of development such as preadolescent childhood. This phase of development is important because efforts to enhance resilience here have preventative potential; children’s emotional experiences are also changing, which may make them more receptive and amenable to acquiring, learning, and consolidating lifelong adaptive strategies for managing emotions.

A study of emotional resilience as it emerges across middle and late childhood into early adolescence and the factors that predict early resilience trajectories would be an invaluable addition to the field for several reasons. First, early signs of reduced emotional resilience could predict reduced well-being and increased mental health problems and their impact in youth, enabling us to identify those who are less well-equipped to manage the challenges and opportunities of adolescence—and in turn, across the lifespan. Second, understanding the factors contributing toward the development of emotional resilience could help with the development of preventative programs and the planning of resources to reduce negative outcomes across the lifespan. Finally, as resilience reflects “the capacity of a dynamic system to adapt successfully to disturbances that threaten system function, viability, or development,” it is likely that its nature and core components vary in childhood compared to adolescence and adulthood. More specifically, preadolescent childhood is a period when emotional experiences are becoming more complex, varied, and at times, more intense [8]. These age-based differences may mean that the factors contributing to resilience change between childhood and adolescence, as they begin to stabilize and consolidate. Yet, these more enriched experiences may also allow a more plastic period for children to learn and practice adaptive strategies for managing stronger, more intense emotional experiences.

A better understanding of emotional resilience in mid-to-late childhood would therefore allow us to propose developmentally sensitive theories of resilience. The Youth Resilience Unit is based at Queen Mary University of London—in the diverse and relatively economically deprived area of East London. The university has a commitment to its location and surrounding community, and it is an area that is underresearched; therefore, it has a focus in terms of understanding the development of resilience in this often challenging sociocultural environment. In the 2021 census, East London was found to be much more culturally diverse in relation to the whole of England and Wales, with a much higher proportion of Asian (32.6% vs 9.3%), Black (14.6% vs 4%), mixed (5.6% vs 2.9%), and other (5.1% vs 2.1%) ethnicities and significantly lower in those who identified as White (42.1% vs 81.7%) [9]. In terms of economic activity, East London also has higher levels of self-employment or no employment (10.1% vs 7.9%), students with no employment (9% vs 6.3%), unemployed (4.7% vs 2.8%), and with much lower proportion of retirees (8.6% vs 21.6%). Having a young and the most diverse population in the United Kingdom while also being historically underserved in research makes East London the perfect location for the timely addition of a new cohort study.

The Development of Emotional Resilience (DEER) study is a new (accelerated) longitudinal cohort of preadolescent children (aged 7-11 years at recruitment) residing in East London to address questions relating to (1) the early development of resilience, (2) differences across individuals in resilience trajectories, and (3) factors/resources that contribute toward resilience trajectories.

### Objectives

We have 3 primary objectives in the DEER study. These are to explore how preadolescent children growing up in deprived areas of London may operationalize resilience, evaluate whether there are differences in the development or trajectories of resilience among our target population, and understand what contributes to resilience pathways over time. Additionally, our research aims to better understand the psychometric properties of resilience measures used in a preadolescent sample and assess the feasibility of developing a longitudinal cohort study of preadolescent children in East London.

## Methods

### Recruitment and Study Design

#### Study Design

The DEER study is an observational cohort study that uses an accelerated longitudinal design. An accelerated longitudinal design recruits participants from different aged cohorts and follows them up [10], allowing both a within-time assessment of cross-age differences (cross-sectional age effect) and a cross-time assessment of within-person differences (longitudinal time effect). We will aim to enroll approximately 1200 children across UK school years 3, 4, and 5 (aged 7-11 years at recruitment) attending primary schools in East London. Children will be assessed at least once a year until they reach the end of their first term of secondary school. Parents/carers and teachers will be asked to complete questionnaires to complement children’s self-reported measures annually.

#### Settings and Participants

Schools were contacted from a database containing all schools located in the broad geographical area of East London. Of the schools approached, a total of 10 primary schools in East London across 5 boroughs were recruited. These boroughs (Waltham Forest, Havering, Redbridge, Newham, and Tower Hamlets) include among the most densely populated, socioeconomically, and ethnically diverse areas in London [11].

#### Consenting Process

Prior to enrolment, research assistants conducted an in-school talk aimed at children from the targeted age group about the DEER study. After the talk, they distributed information sheets to children and their parents/carers. Initially the ethics committee recommended that the consenting process be opt in, that is, in addition to assent collected from children, parents or guardians needed to provide written consent in order for a child to take part. When it became apparent that enrolment was very low (by November 2022, only 6.9% (131/1898) of the consent forms were returned signed) and potentially biased in favor of parents and families who were better resourced, the ethics committee allowed for an opt out process. This means that for the 10 recruited schools, 6 are opt-in only, 1 began with opt-in processes but then agreed to participate using opt-out procedures, and the remaining 3 are opt-out only schools. For opt-out schools, parents were asked to return a form or contact the school or research team to indicate they did not want their child to take part, and then no data were collected from the opted-out children. The team liaised with schools to ensure that only students who met our inclusion criteria were enrolled in the study. Because most of the data are self-reported, some of our measures are not suitable for students who have been diagnosed with an intellectual disability disorder.

#### Participant Inclusion Criteria

In order to be enrolled in the study, children must be (1) attending a primary school in East London, (2) in school years 3 to 5 (at recruitment), (3) able to understand written and spoken English, (4) willing and able to provide assent, and (5) able to obtain parental/carer consent for opt-in schools.

#### Participant Exclusion Criteria

To participate in this study, children must not be diagnosed with an intellectual disability disorder.

#### Sample Size

Based on the planned analyses, the target recruitment was 1200 children in school years 3-5 (age 7-11 years). This sample size provides (1) 94% power to detect correlations as small as 0.10 (2-tailed), *P*<.05 between resilience measures and correlates and (2) the opportunity to compare groups high and low on a psychological or social factors (eg, top and bottom 20% of the sample on attention control) or on a resilience measure and to detect even small effects (eg, Cohen *d*=0.30) at 90% power, 2-tailed, *P*<.05.

Importantly, this sample size will enable us to use novel data-driven analytic approaches to identify subpopulations with different resilience trajectories across time and to assess the predictive value of different psychosocial variables (main effects, interactions, mediation effects) on resilient trajectories by using multinomial logistic regression. This will also allow us to use other advanced quantitative analyses, including structural equation modelling (to explore mediation and moderation effects), a combination of exploratory and confirmatory factor analysis (to verify the factor structure of selected questionnaires), and network analysis to explore associations between individual items of questionnaires.

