## Results

Barts Charity awarded a grant to the Faculty of Medicine and Dentistry, Queen Mary University of London, on March 30, 2020, to establish the Youth Resilience Unit. The Unit was established on March 1, 2021. This core funding also provided support for this study. Ethics approval (QMERC22.251) was granted by the Queen Mary research ethics committee on June 27, 2022. Study recruitment commenced from October 2022 and continued till December 2023. Baseline testing commenced in October 2022 and continue till December 2023; 873 students were enrolled at baseline. Follow-up is anticipated to continue at least annually until June 2027. Baseline and follow-up questionnaires will provide evidence regarding the acceptability and feasibility of conducting a longitudinal cohort study in primary schools in East London.

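### The stated 94% and 90% power are right for the target of 1200, but the article reports enrolment closed at 873, where they are about 84% and 80%

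*Protocol article*

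**What the plan says.** The Sample Size section of the protocol article states that "the target recruitment was 1200 children in school years 3-5". It then gives two power statements for that number. The first is "This sample size provides (1) 94% power to detect correlations as small as 0.10 (2-tailed", at the 5% level. The second concerns groups high and low on a factor, with the "top and bottom 20% of the sample on attention control" as the example, and says that the study can "detect even small effects (eg, Cohen *d*=0.30) at 90% power", two-sided at 5%. The next paragraph says that the same sample size will make the trajectory, multinomial, structural equation, factor and network analyses possible.

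The Results section reports "Study recruitment commenced from October 2022 and continued till December 2023" and then "873 students were enrolled at baseline". The abstract gives the same dates and count, and the Procedures section places all baseline questionnaires in the same period. The abstract's Methods paragraph and the Study Design section still give about 1200 as a forward-looking aim. The section on weaknesses discusses self-report, parent and teacher response, and fatigue, but not the shortfall. Power for 873 appears nowhere.

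**The concern.** The only power statement in the article rests on a sample size that the article itself shows was not reached. The sentence on the target is in the past tense, but the power claims are in the present and the claims about the advanced analyses are in the future. They therefore read as what this cohort can do, although baseline enrolment was already closed and known.

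Specific analyses are deferred to separate preregistrations, so this section is the natural place for later papers to take a power figure from. If they carry over 94% and 90%, they will understate the chance of missing effects of the size named.

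**Working it through.** **Inputs, all from the protocol article**
- Target 1200 (Sample Size); enrolled 873 (Results). Shortfall: 1200 − 873 = 327, and 327/1200 = 27%.
- r = 0.10 and d = 0.30, two-sided 5% (Sample Size), so the critical value is 1.960.
- Extreme fifths as the example comparison: 0.20 × 1200 = 240 per group; 0.20 × 873 = 174.6, so 174 to 175 per group.

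**Step 1. Reproduce the stated figures at 1200**

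Correlation, by Fisher's z: power = Φ(√(n − 3) × atanh(r) − 1.960), with atanh(0.10) = 0.1003.
- √1197 × 0.1003 = 3.471; 3.471 − 1.960 = 1.511; Φ(1.511) = 93.5%. The noncentral t gives 93.6%. Stated: 94%.

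Two groups of m children each, normal approximation: power = Φ(d × √(m/2) − 1.960).
- 0.30 × √120 = 3.286; 3.286 − 1.960 = 1.326; Φ(1.326) = 90.8%. The noncentral t gives 90.7%. Stated: 90%.

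Both stated figures reproduce, so the method is not in dispute.

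**Step 2. Same formulas at 873**
- Correlation: √870 × 0.1003 = 2.960; 2.960 − 1.960 = 1.000; Φ(1.000) = 84.1%. The noncentral t gives 84.3%.
- Two groups: 0.30 × √(174.6/2) = 2.803; 2.803 − 1.960 = 0.843; Φ(0.843) = 80.0%. The noncentral t with 174 or 175 per group gives 79.7% to 79.9%.

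**Step 3. Effects detectable at the stated power with 873**
- r at 94%: tanh((1.960 + 1.555)/√870) = tanh(0.1192) = 0.119.
- d at 90%, 174 per group: (1.960 + 1.282) × √(2/174) = 0.348, about 0.35.

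| | Stated | Recomputed at 1200 | At 873 | Detectable at stated power, 873 |
|---|---|---|---|---|
| r = 0.10 | 94% | 93.5% | 84.1% | r = 0.119 |
| d = 0.30, extreme fifths | 90% | 90.8% | about 80% | d = 0.35 |

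The chance of missing an effect of the named size goes from 6.5% to 15.9% for the correlation and from about 9% to about 20% for the group comparison.

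**Step 4. Illustration only: retention**

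The article gives no retention rate. If 90%, 80% or 70% of the 873 were analysed, and nothing else changed, power would be about 80%, 75% or 70% for r = 0.10 and about 76%, 71% or 65% for d = 0.30. These rates are assumptions, and the finding does not depend on them.

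**The case against.** The strongest reply is that the section labels its basis. It names 1200 as a target, the power figures are correct for that target, and reporting the planning calculation is normal practice. The abstract and the Results section disclose 873, so nothing is hidden. The study has no single confirmatory test, each hypothesis-driven analysis is to be preregistered, and the available number can be stated there. The group comparison is explicitly an example.

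Much of this stands. There is no arithmetic error at 1200, and keeping the planning calculation is proper. The 80% figure holds only for the illustrative fifths. What does not stand is leaving those figures as present and future capability after enrolment had closed. A reader who sees 873 is given the count but not its consequence.

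Three stronger readings are tempting, and the documents do not support them:
- A reader might infer that 873 is too few for the trajectory, structural equation or network analyses. The article gives no minimum number for them, and power for a single correlation does not measure power for those models.
- A reader might infer that null results will be taken as evidence of absence at 94% or 90% power. Nothing in the article says so.
- A reader might infer that the missing allowance for attrition makes the power figures wrong. They name no follow-up time point, and a condensed article may leave that allowance to the full protocol.

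**Conclusion.** The point holds as an inconsistency between the stated power and the achieved sample. The two examples have about 84% and 80% power at 873, roughly 9 to 11 percentage points below what the same formulas give at 1200 (93.5% and 90.8%). Equivalently, the detectable effects at the stated power move from 0.10 to about 0.119 and from 0.30 to about 0.35.

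These figures assume that all 873 children contribute complete data, that children are independent although they come from 10 schools, and that the comparison groups are the extreme fifths. They are therefore best read as upper values. The article gives neither an intraclass correlation nor a retention rate, so the further loss cannot be fixed from it.

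Severity is moderate. Both examples keep power close to or above 80% at baseline, and no design choice or decision rule in the article turns on the difference.

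**What to change.** In the Sample Size section, keep 1200 and its power figures as the planning calculation, in the past tense, and add the achieved sample. For example:

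> The planned sample was 1200, which would have given 94% power for r = 0.10 and 90% power for d = 0.30 between extreme fifths. Enrolment closed with 873 children. With complete data and independent observations, this gives about 84% and 80% power respectively; r = 0.119 is detectable with 94% power and d = 0.35 with 90%. These are upper values, before allowance for clustering within schools and for attrition.

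Reword the following paragraph so that its statement on the advanced analyses refers to the 873 enrolled. Put the aim of 1200 in the abstract's Methods paragraph and in Study Design into the past tense, and mention the shortfall among the weaknesses. A line on power under stated retention rates is optional and should be labelled as an assumption.

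The cost is a few sentences and less favourable figures. No change to design, data collection or enrolment is needed.

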#### Parents’/Carers’ Measures

Table 3 shows the list of measures that parents/carers will complete about their children [43-49].

**Table 3 table3:** List of measures that parents/carers will complete about children.

Name of the scale	Brief description	Style of administration
Demographics and socioeconomic status questionnaire	Questions will ask about the child’s date of birth, sex, ethnicity, country of birth, and number of siblings. We will also include questions about socioeconomic status, child’s religion, family migration status, family structure (ie, foster family, single parent, nuclear family), carers’ relationship to the child (ie, biological, foster or adoptive mother or father), household number, the child’s birth order, diet type they primarily follow, if the child has ever been in the care of local authority (ie, in foster or residential care), and if the child or anyone in their immediate family has ever been formally diagnosed with a mental health disorder. Socioeconomic status questions will include items relating to the carers’ education, occupation, material possessions, whether the child receives free school meals, type of accommodation, and post code (to ascertain material deprivation index).	Online platform
Patient Health Questionnaire 15 [43]	These measures link to physical health problems, including any chronic illness or disability, pain, fatigue, and sleep. For the Patient Health Questionnaire, we will only use questions relevant to physical health problems.	Online platform
Child Health Utility instrument 9D [44]	The Child Health Utility instrument is a pediatric generic preference-based measure of health-related quality of life—we will be using a proxy version for parents to complete. We will also be using questions formulated in-house to ascertain key factors such as hospitalization rates and birth weight.	Online platform
The Strengths and Difficulties Questionnaire [45]	The questionnaire asks about the parents or carers report on their child emotional symptoms, conduct problems, hyperactivity/inattention, peer relationship problems, and prosocial behavior.	Online platform
Arts Council Questionnaire The Taking Part Survey [46]	The survey collects information about children and adults’ attendance at a wide variety of arts events, museums, galleries, libraries, and heritage sites. It also asks about participation in creative activities and sport and motivations and barriers to engagement.	Online platform

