### Weaknesses in This Study

This study relies heavily on self-report from young children, and it is not always clear how reliable or valid this method is in children of this age. We have tried to balance this by including measures by teachers and parents. However, parents are notoriously difficult to engage in this process, and this may result in lower levels of data from parents. Teachers also may be less responsive due to their many responsibilities and limited time to complete assessments. The large number of child assessments may also cause participant fatigue, particularly in a school setting. This may lead to nonrandom missingness in the results.

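### The 94% power for r=0.10 is worded to cover all correlates, but correlates collected only from parents will have fewer records than the 1200 behind that figure

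*Protocol article*

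**What the plan says.** In Methods, Sample Size, the article states that "the target recruitment was 1200 children in school years 3-5 (age 7-11 years") and attaches two power figures to that number. The first is "94% power to detect correlations as small as 0.10 (2-tailed), *P*<.05 between resilience measures and correlates". It carries no restriction by informant and no allowance for non-response. The second, 90% power for Cohen d=0.30, is for the chance to "compare groups high and low on a psychological or social factors", or on a resilience measure. The example given is the "top and bottom 20% of the sample on attention control".

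Under Parents’/Carers’ Measures, "Table 3 shows the list of measures that parents/carers will complete about their children" through an online platform. Several of these variables appear in no child or teacher table: socioeconomic status (including the postcode used for a deprivation index), ethnicity, family structure, life events and parenting style.

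Weaknesses in This Study says that "parents are notoriously difficult to engage in this process, and this may result in lower levels of data from parents". The Results section reports 873 children enrolled at baseline.

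**The concern.** A correlation needs both variables on the same child. For a parent-only correlate, the analysed n is therefore the number of children with a parent questionnaire, not the number enrolled. Enrolment does not guarantee that questionnaire. The Consenting Process section describes three opt-out-only schools and one that moved to opt-out, where a child can take part without any action by the parent.

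Understanding what contributes to resilience pathways is one of the three primary objectives. The parent-only block holds deprivation and adverse life events, which are prominent in the article's own rationale. If the 94% is taken at its printed scope, a null finding for one of these variables would seem better supported than it is.

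**Working it through.** **Inputs.** From Sample Size: N=1200, r=0.10, two-sided alpha 0.05, stated power 94%; also d=0.30, top against bottom 20%, stated power 90%. From Results: 873 enrolled. The parent response rate is not given anywhere, so 80%, 60% and 40% are assumed to show a range.

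**Step 1: reproduce the stated figures.** For a correlation, the Fisher z approximation is power = Φ(atanh(r)·√(n−3) − 1.96), with atanh(0.10) = 0.1003.

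- n=1200: 0.1003 × √1197 = 3.471; 3.471 − 1.96 = 1.511; Φ = 93.5%. This agrees with the stated 94%.
- d=0.30 with 20% of 1200 = 240 per group: 0.30 × √(240/2) = 3.286; 3.286 − 1.96 = 1.326; Φ = 90.8%. This agrees with the stated 90%.

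Both figures need a complete record for each of the 1200 children.

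**Step 2: the same formula at the n available for a parent-only correlate.** Here n = children × assumed parent response, rounded down.

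| Parent response (assumed) | n from 1200 | Power, r=0.10 | n from 873 | Power, r=0.10 |
|---|---|---|---|---|
| 100% | 1200 | 93.5% | 873 | 84.1% |
| 80% | 960 | 87.4% | 698 | 75.3% |
| 60% | 720 | 76.6% | 523 | 62.9% |
| 40% | 480 | 59.2% | 349 | 46.3% |

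The 84.1% at 873 comes from the enrolment shortfall alone and applies equally to child-reported correlates. Only the fall down each column is due to parent non-response.

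**Step 3: how much non-response the claim tolerates.** Power of 92%, two points below the stated 94%, needs n = ((1.960 + 1.405)/0.1003)² + 3 ≈ 1128. As 1128/1200 = 94%, about 94% of parents would have to reply even if the full target had been enrolled.

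**Step 4: detectable correlation.** r = tanh((1.960 + z)/√(n−3)), with z = 0.842 for 80% power and 1.282 for 90%.

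- n=523: 2.802/22.80 gives r ≈ 0.12 at 80% power; 3.242/22.80 gives r ≈ 0.14 at 90%.
- n=349: 2.802/18.60 gives r ≈ 0.15 at 80% power; 3.242/18.60 gives r ≈ 0.17 at 90%.

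**The case against.** The strongest reply is that nothing is miscalculated. Both figures reproduce, the section is a planning statement, and the article is open about weaker parent data. It lists parent completion among its feasibility counts and leaves missing data to each paper's preregistration. Parents are asked every year and paid each time, so fixed items such as ethnicity could be filled in from a later wave. Since no response rate is given, the loss could also be modest: at 80% of 1200, power is still 87%.

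Most of that stands, and it limits the point to the scope of the wording. It does not rescue that scope. Disclosing fewer parent records in the Weaknesses section does not change a power statement that assumes there are none missing. Later waves help only with stable items. Imputing a variable that is absent for want of a whole questionnaire does not in general restore full-sample information.

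Three stronger readings are tempting and should be resisted.

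- **That the 90% figure is also claimed for every correlate.** It is not. It concerns groups on psychological or social factors, or on a resilience measure. Table 2 lists such factors as child-completed, and the resilience scales in Table 1 are child self-report. The caveat reaches this figure only where a grouping factor is parent-reported.
- **That everything in the parent questionnaire is parent-only.** Physical health is not: children complete the Somatic Complaints List and have height and weight measured.
- **That parent- and child-reported factors will be ranked by significance.** The article proposes nothing of the kind.

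**Conclusion.** The point holds as one of scope. The 94% is correct for 1200 complete pairs, but the phrase "between resilience measures and correlates" extends it to parent-only variables for which the article itself anticipates fewer records.

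The size depends on a response rate that the article does not report. Under the assumed 80% to 40%, power for r=0.10 lies between about 87% and 59% at 1200 children, and between about 75% and 46% at the 873 enrolled. A reader might infer that the claim is shown to fail by a known amount for the whole parent block. The article does not support that: only the direction is established, together with the fact that the stated figure tolerates very little non-response. The signed consent returns of 6.9% (131/1898) by November 2022 concern a different form and should not stand in for a questionnaire response rate.

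The drop from 94% to 84% through enrolling 873 is a separate matter. Correcting for it alone would still overstate power for parent-only correlates unless every parent replied.

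**What to change.** In Sample Size, limit the 94% statement to correlates measured on the child, at n=1200. Add a separate sentence for parent-only correlates, based on the observed number of baseline parent questionnaires. It should give either the power for r=0.10 or the detectable correlation with its power level named. For example, at n=523 it would read r of about 0.12 at 80% power or 0.14 at 90%; at n=349, about 0.15 or 0.17. Note that the 90% figure for d=0.30 carries the same caveat where the grouping factor is parent-reported.

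The count should be easy to obtain: baseline questionnaires were administered up to December 2023, and parent completion is already among the planned feasibility counts. No new data or participants are needed. The cost is a less favourable stated figure for parent-reported factors.
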